**Methods:**

A randomized, 2-arm clinical trial will be conducted with patients with OSA from the Hospital, Mexican Social Security Institute (Instituto Mexicano del Seguro Social) in Mexico. Patients will be randomly included in the group with MD adapted to Mexican foods. With a personalized diet plan adapted from the Mediterranean diet, prototype menus with Mexican foods adapted from the MD will be included for a higher consumption of fruit, vegetables, fiber-rich cereals, and reduction of red meat. In addition to an illustrative plate to improve adherence. The standard diet (SD) group will receive standardized nutritional counseling for patients with OSA. Fasting blood samples will be drawn after 6 and 12 months to identify glucose levels and lipid profiles. Anthropometric and body composition measurements will be taken, and adherence to diet will be recorded after 3, 6, and 12 months. Sleep quality, physical exercise, and life quality will be recorded basally and after 12 months. A multivariate logistic regression analysis will be performed, including the achievement of metabolic indicator control goals, sleep quality, and quality of life as outcome variables. This analysis will be adjusted for other variables that may be statistically significant in the bivariate analysis, such as sex, age, and comorbidities, among others. Statistically significant differences between groups will be considered when the value of *P*<.05.

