**Results:**

The protocol was authorized in 2024, and funding is being sought for patient follow-up. All 120 patients (60 per group) will be included in 2025; recruitment will begin in March 2025. The clinical trial is expected to be completed in April 2026.

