## Methods

### Study and Population Assignment

A randomized, 2-arm clinical trial will be conducted with patients with OSA from the Regional Hospital, Mexican Social Security Institute (Instituto Mexicano del Seguro Social [IMSS]) in Mexico City with a 12-month follow-up.

The sample size was calculated using the formula for difference in proportions, considering a CI of 95% and a power of 80%. Weight loss is expected in 58% of the sample corresponding to the group given an MD adapted to the Mexican population and in 30% of the group consuming a standard diet, as previously reported in the literature. A sample size of 49 patients per group was obtained and, considering losses of 20%, the total number of patients will be 120 [16].

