### Statistical Analysis

The statistical analysis of the data will be carried out using SPSS (version 27; IBM Corp). The study population will be described using the background, clinical, and pathological variables to characterize the sample of participants with OSA. The Kolmogorov–Smirnov test will be used to identify the distribution of quantitative variables. For variables with normal distribution measures of central tendency and dispersion will be estimated. For variables with a free distribution mean and IQR will be used. Measures of frequency and percentages will be used for sociodemographic and clinical qualitative variables, as well as those of patient proportion with and without glycemic control, and with and without cognitive impairment. A chi-square test will be used to compare the effect of MD versus SD on parameters of control and uncontrol of metabolic risk indicators. Depending on the data distribution, a Student *t* test will be used to compare quantitative variables with parametric distribution between groups, and a Mann-Whitney *U* test will be conducted for free-distribution variables. A multivariate logistic regression analysis will be performed, including the achievement of metabolic indicator control goals, sleep quality, and quality of life as outcome variables. This analysis will be adjusted for other variables that may be statistically significant in the bivariate analysis, such as sex, age, and comorbidities, among others. Statistically significant differences between groups will be considered when the value of *P*<.05.

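### Logistic-model covariates are chosen by bivariate significance from an open list not limited to baseline, and follow-up CPAP use is added, so what the adjusted odds ratio estimates is not fixed in advance

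*Protocol article*

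**What the plan says.** The Statistical Analysis section plans a multivariate logistic regression "including the achievement of metabolic indicator control goals, sleep quality, and quality of life as outcome variables". The models are to be "adjusted for other variables that may be statistically significant in the bivariate analysis, such as sex, age, and comorbidities, among others". The Methods part of the abstract repeats the rule: "This analysis will be adjusted for other variables that may be statistically significant in the bivariate analysis".

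Three further statements bear on it:

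- The last paragraph of the Discussion's Anticipated Findings says CPAP use will be recorded at the follow-up visits and entered in the multivariate analysis. That covariate is named outside the significance screen.
- Table 2 schedules physical activity, three-day food records and MEDAS both at baseline and after randomisation.
- The Statistical Analysis section also plans unadjusted comparisons of the arms: chi-square for control status, and t or Mann-Whitney tests for quantitative variables.

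The section gives P<.05 for differences between groups. It states no separate threshold for the screen, and does not say whether bivariate means association with the outcome or with the arm.

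**The concern.** In a randomised trial, covariates are adjusted for because they predict the outcome, and they are named beforehand so that the data cannot choose the model. The stated rule does the reverse, with four consequences:

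- **Chance and analyst choice.** The set is known only once outcome data are seen, and it can differ for every outcome.
- **A shifting target.** An odds ratio changes in meaning with the covariates it is conditioned on, even without confounding. A data-chosen set therefore changes what is estimated as well as its precision.
- **No place for the usual best predictor.** The baseline value of the outcome enters only if it passes the screen.
- **Post-randomisation variables.** Nothing restricts candidates to baseline. CPAP use at follow-up is planned, and follow-up adherence or activity could enter. The diet may affect these, and adherence is something it is meant to change. Conditioning on them can remove part of the effect or bias it.

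The Results section expects differences in the multivariate analysis for control goals, sleep quality and quality of life, so these models will carry conclusions.

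**Working it through.** **1. The plan's own figure.** Inputs from Study and Population Assignment: for the intervention arm, "Weight loss is expected in 58% of the sample corresponding to the group given an MD adapted to the Mexican population"; the assumed rate for the control arm is 30%. Power is 80% and the level 95%, read as two-sided 5%. With mean rate (0.58 + 0.30)/2 = 0.44:

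n = [1.96 × √(2 × 0.44 × 0.56) + 0.842 × √(0.58 × 0.42 + 0.30 × 0.70)]² / 0.28² = 48.1, rounded up to 49 per group.

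This reproduces the plan: "A sample size of 49 patients per group was obtained and, considering losses of 20%, the total number of patients will be 120". For losses, 49/0.8 gives 62 per group and 49 × 1.2 gives 59; the planned 60 lies between.

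**2. Events.** With 60 per group and 20% lost, 48 per arm (96 in all) complete. At the weight-loss rates that is 48 × (0.58 + 0.30) = 42 events. The article gives no rate for any logistic outcome. For assumed overall rates of 20% to 50%, events run from 96 × 0.20 = 19 to 96 × 0.50 = 48.

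**3. Irrelevant covariates entering.** Assume independent candidates screened against the outcome at P<.05. The chance that at least one of k irrelevant candidates enters is 1 − 0.95^k: 23% for k = 5, 40% for k = 10, 54% for k = 15.

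**4. Effect on the analysis.** Simulation with 48 per arm and 2,000 runs per scenario. Assumed: ten independent baseline candidates, three prognostic and seven noise, each screened against the outcome at P<.05. Marginal rates were 58% and 30%, or 44% in both arms under the null.

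| Log-odds per SD | Power, unadjusted | Power, screened | Power, three fixed | Share of gain lost |
|---|---|---|---|---|
| 0.4 | 78.5% | 79.6% | 82.2% | (82.2 − 79.6)/(82.2 − 78.5) = 70% |
| 0.6 | 81.0% | 83.4% | 86.6% | (86.6 − 83.4)/(86.6 − 81.0) = 57% |
| 0.8 | 78.9% | 86.0% | 88.5% | (88.5 − 86.0)/(88.5 − 78.9) = 26% |

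- Type I error with screening was 4.2% to 5.6%. The simulation standard error is √(0.05 × 0.95/2000) = 0.5 points, so no inflation is visible.
- Across the effect and null scenarios, 94 to 127 different covariate sets were chosen per 2,000 runs. The commonest set had a share of 13% to 41%. All three prognostic covariates were chosen in 4% to 56% of runs.
- The significance verdict differed from the fixed model in 1.4% to 5.0% of runs.
- At log-odds 0.6 the mean log odds ratio was 1.20 unadjusted, 1.42 screened and 1.52 fixed. The conditional value built in was 1.425, so the fixed model overshoots somewhat in samples this small. The figures show that the estimate moves with the covariate set; they do not show that one set is more accurate.

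A separate simulation (6,000 runs, four of ten covariates prognostic at 0.4) gave power of 78.4% unadjusted, 78.1% screened and 81.0% fixed. There, with weak predictors, essentially none of the gain was kept.

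No simulation covers post-randomisation covariates, so that bias is not quantified.

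**The case against.** The strongest reply is that little is lost. In the three tabulated scenarios screened power is never below unadjusted power, type I error holds, and the verdict seldom changes. The unadjusted tests do not depend on the screen at all. This stands, and it limits the point to the adjusted models.

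Four stronger readings are tempting and are not supported:

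- **That these models will have about 42 events.** That figure uses the weight-loss rates among completers; the logistic outcomes have no stated rate.
- **That screening forfeits the whole gain from adjustment.** It came close in one weak-predictor scenario, but kept part of the gain in the others.
- **That screening inflates false positives.** With baseline candidates it did not visibly do so.
- **That adherence will enter the models.** The text permits it; only follow-up CPAP use is announced.

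It is also fair that the screen is ambiguous. The only bivariate tests described compare the arms, whereas the calculations assume screening against the outcome. That limits the figures but does not rescue the rule. Screening against arm would pick up chance imbalances and any follow-up variable that the diet changes.

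An unseen analysis plan is no answer: one that named fixed covariates would contradict the rule stated here.

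**Conclusion.** The point holds for the adjusted logistic models only. The stated rule leaves the covariate set, and with it the meaning of the adjusted odds ratio, to chance. It guarantees no place to the baseline outcome, and together with the Discussion it brings a post-randomisation variable into the model.

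Under the assumed scenarios the cost is modest: 2.5 to 3.2 points of power against fixed covariates. That comparison favours the fixed set, because it contains exactly the prognostic variables. The larger risks are an estimate open to choice after the data are seen and the unquantified bias from follow-up variables. The change is worth making because it is nearly free. Confidence is high in the defect and lower in its size.

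**What to change.** In the Statistical Analysis section and in the Methods part of the abstract, replace the screening sentence with:

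*Each logistic model includes arm, the baseline value (or baseline control status) of that outcome, age and sex, whatever their P values; no variable measured after randomisation is included in this model.*

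Reconcile the Discussion with this. Follow-up CPAP use belongs in a separate analysis labelled exploratory. If a CPAP covariate is wanted in the main model, use a baseline measure. Because CPAP use is an inclusion criterion, a yes/no variable would hardly vary, so the measure would need to be graded; the article does not say that one is collected.

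The list has four terms. By the common rule of thumb of ten events per term, 42 events support about four. Near 19 events even this list is tight, and any shorter list should also be fixed in advance.

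The cost is a few sentences in three places. Age, sex and the baseline outcome values are already collected. The Results section places the data analysis in February 2026, and the change is credible only if made before outcome data are examined.

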### Ethical Considerations

This clinical trial was submitted to the Ethics and Research Committee at HGR 1 “[name] Sánchez Navarrro,” IMSS (registry number R-2024-3609-055). The protocol was reviewed twice for the corresponding modifications related to methodological aspects. The researchers will provide each participant with written consent, describing all the procedures of the clinical trial, the risks, and benefits; this consent form clarifies that the patient is free to not participate or to withdraw from the research without affecting their care at the institution. All participant information collected in the research will be kept confidential, and data will be reported anonymously. Participants in this research will not receive any financial compensation.

The protocol was registered at ClinicalTrials.gov (NCT06782737). The aim of the study, risks, and benefits will be explained in detail to the participants who will freely chose to take part in the trial. They will provide written consent describing each procedure in the trial and respect to information privacy. All the researchers participating receive annual training regarding better clinical practices related to research.

## Results

The protocol was approved in 2024, and funding is being sought for patient follow-up, patient inclusion, and execution of RCT in 2025. Currently, 50 patients have been recruited, 28 in the group with a Mediterranean Diet Adjusted Using Mexican Food and 27 in the group with an SD. The data analysis with the expected results will be carried out in February 2026.

It is expected that there will be differences in the intervention groups of patients with OSA enrolled in the study: measurement of blood pressure, measurement of sleep variables, measurement of biochemical indicators, anthropometric and body composition measures, measurement of sleep quality, and measurement of quality of life. We expect to find in patients with MD a higher proportion of cardiometabolic indicators in control, compared with patients in the group with SD. We expect to find differences in multivariate analysis in control goals of cardiometabolic indicators, quality of sleep and quality of life of patients.

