#### Biochemical Indicator Measurement

Venous blood samples will be taken after fasting for 8-10 hours to measure glucose, lipid profile (cholesterol, triglycerides, high-density-lipoprotein cholesterol, and low-density-lipoprotein cholesterol). Measurements will be recorded during the first consultations and after 6 and 12 months.

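### The analysis (February 2026) and completion (April 2026) dates do not fit recruitment from March 2025 with 12-month follow-up: on nominal dates nobody has a 12-month visit by the analysis date

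*Protocol article*

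**What the plan says.** Four statements in the protocol article set the calendar.

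- Abstract, Results, on enrolment: "All 120 patients (60 per group) will be included in 2025; recruitment will begin in March 2025".
- Abstract, Results, on the end of the trial: "The clinical trial is expected to be completed in April 2026".
- Methods, Study and Population Assignment: a randomised two-arm trial "in Mexico City with a 12-month follow-up".
- Results: "The data analysis with the expected results will be carried out in February 2026". The next paragraph lists what is expected: differences between the groups in blood pressure, sleep variables, biochemistry, anthropometry and body composition, sleep quality and quality of life, and multivariate results on control goals.

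On when outcomes are measured, the Quality of Life Measurement section and Table 2 place the Quebec Sleep Questionnaire at baseline and 12 months only. For glucose and lipids, the Biochemical Indicator Measurement section says "Measurements will be recorded during the first consultations and after 6 and 12 months", and the abstract's Methods also name 6 and 12 months. Table 2 and the Follow-Up and Study Procedures section show laboratory data at baseline and 12 months only.

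On progress, the Results section reports "50 patients have been recruited, 28 in the group with a Mediterranean Diet Adjusted Using Mexican Food and 27 in the group" on the standard diet.

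**The concern.** The analysis is dated before the earliest day on which any patient can complete the planned follow-up, and also before the trial's own stated completion. The February 2026 entry does not read as a baseline report, because the results anticipated straight after it are the outcome comparisons between the arms.

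If the date were followed, the 12-month comparison would have no nominal 12-month data. Quality of life would have no post-baseline value in either arm. Under Table 2 the same would be true of glucose and lipids, which are among the primary outcomes; under the text and the abstract, 6-month laboratory values would exist for those who had reached that visit. Waiting until April 2026 would help only with the earliest enrolees, so a comparison at that point would rest on part of the sample for which the trial was sized.

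**Working it through.** **Inputs**

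- First possible enrolment: 1 March 2025 (abstract, Results).
- Enrolment period: within 2025, so 31 December 2025 at the latest (abstract, Results). No closing month is given.
- Follow-up: 12 months (Methods, Study and Population Assignment).
- Analysis: February 2026, so 28 February 2026 at the latest (Results).
- Completion: April 2026, so 30 April 2026 at the latest (abstract, Results).
- Sample size: 58% versus 30%, 95% confidence, 80% power, 49 per group, 120 in total (Methods).

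**Calendar check**

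Twelve-month visit = enrolment date + 12 months.

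| Enrolled | Nominal 12-month visit | Days of follow-up on 28 Feb 2026 | Days of follow-up on 30 Apr 2026 |
|---|---|---|---|
| 1 March 2025 | 1 March 2026 | 364 | past 12 months |
| 21 August 2025 (publication date) | 21 August 2026 | 191 | 252 |
| 31 December 2025 | 31 December 2026 | 59 | 120 |

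- By 28 February 2026: 0 of 120 patients at the nominal 12-month visit.
- By 30 April 2026: only patients enrolled by 30 April 2025. For the trial to be complete then, all 120 would have to be enrolled in the first two months.
- If enrolment ends in December 2025, the last 12-month visit falls in December 2026.

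**The plan's own sample size**

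With p1 = 0.58, p2 = 0.30, mean 0.44, two-sided alpha 0.05 and no continuity correction:

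n = [1.96 × √(2 × 0.44 × 0.56) + 0.8416 × √(0.58 × 0.42 + 0.30 × 0.70)]² / 0.28² = 48.1, rounded up to 49 per group.

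This reproduces the stated 49, at which power is about 81%. The sample size is not in question here.

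**What April 2026 completers alone would give**

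No section plans such an analysis; this only measures what the stated completion date would leave. The accrual pattern is not in the article, so two assumptions are shown.

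- Even accrual from March to December 2025 (10 months): 2/10 × 120 = 24 patients, or 12 per arm.
- All of the reported recruits (28 + 27) enrolled by the end of April 2025: about 27 per arm. This is a generous case. Spread evenly from 1 March to the publication date (174 days), 55 recruits would put only 55 × 61/174 ≈ 19 before the end of April.

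Power (normal approximation) = Φ{[0.28 − 1.96 × √(2 × 0.44 × 0.56/n)] / √[(0.58 × 0.42 + 0.30 × 0.70)/n]}.

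- n = 12: Φ[(0.28 − 1.96 × 0.2026)/0.1944] = 27%. The exact calculation for the uncorrected chi-square test gives 32%.
- n = 27: Φ[(0.28 − 1.96 × 0.1351)/0.1296] = 55%. The exact calculation gives 53%.

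**Recruitment count**

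28 + 27 = 55, not 50. On either figure, fewer than half of the 120 had been recruited at the time of writing, and at least 120 − 55 = 65 were still to come.

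**The case against.** The strongest reply is that these are projected calendar dates. The Statistical Analysis section ties no test to a date, and the visit schedule fixes collection at 12 months. A team that follows the schedule will simply analyse later, with the same endpoint, sample size and tests. This is true, and it is why the repair is cheap. It does not make the printed dates compatible.

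The second reply concerns how absolute the zero is. The margin for a patient enrolled on 1 March 2025 is one day. An ordinary early visit window could admit a few of the first enrolees, and a condensed article may leave windows to the full protocol. The start is also a forecast: "recruitment will begin in March 2025". The count is therefore one of nominal dates. Neither point brings more than the earliest patients into a February 2026 analysis.

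A reader might infer more than the article supports:

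- *That February 2026 is declared the final analysis.* The article does not use that word. It describes no other analysis, however, and the results anticipated are the trial outcomes.
- *That an interim look is intended.* None is described. A between-arm comparison made in February 2026 would be an early look in effect, but that follows only if the date is kept.
- *That the trial would fall back on a 3-month comparison.* For anthropometry and laboratory data this is not available: Table 2 gives the standard diet arm only a phone call and the sleepiness scale at 3 months.
- *That glucose and lipids have no 6-month value.* Table 2 says so, but the abstract and the biochemistry section say the opposite. That is a contradiction of its own.
- *That five randomised patients were dropped from the count.* Nothing shows this; a mistyped total explains 50 against 55 equally well.
- *That power will be about 30%.* That figure belongs to one accrual assumption.

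**Conclusion.** The point stands in this form: the recruitment start, the 12-month follow-up, the analysis date and the completion date cannot all be right. On nominal dates, 0 of 120 patients have 12-month data by the end of February 2026. This needs no accrual assumption, only that recruitment did not start before March 2025 and that no early visit window applies. By the end of April 2026, only patients enrolled in March or April 2025 could have the endpoint.

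The loss of power is conditional. It is about 27-32% with 12 per arm and up to about 55% with 27 per arm, against the stated 80%, and it applies only if April 2026 completers alone were analysed.

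The mismatch of 50 with 28 + 27 is a separate arithmetic error and adds no weight to the timeline point.

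**What to change.** 1. Replace both the analysis date and the completion date. Tie the between-arm outcome analysis to the last randomised patient's 12-month visit and completed data cleaning, which means December 2026 or later if enrolment ends in December 2025.
2. State that no between-arm outcome comparison is made before then. If a report in February 2026 is wanted, label it as baseline data only.
3. State the actual recruitment start and the planned close, so that the dates can be checked.
4. Separately, correct the recruitment total against the randomisation list (50 stated, 55 by arm).

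The cost is new dates, a sentence or two, and a later result. No extra patients or visits are needed.
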